#### Association of CLAS with depth of anesthesia

3.7.2

Depth of anesthesia will be evaluated using the BIS index, an EEG-derived index validated for intraoperative monitoring (Connor, 2022; Rampil, 1998). BIS index values will be compared across *in-phase*, *anti-phase*, and *sham* blocks using repeated-measures ANOVA and pairwise paired *t*-tests with Holm–Bonferroni correction, to control for multiple comparisons. To probe the relationship between the BIS index and underlying cortical dynamics, correlation analyses will be run between BIS values and *δ*-wave features (amplitude, slope, spectral power), building on prior evidence that BIS partly reflects the presence and strength of slow oscillatory activity (Akeju and Brown, 2017; Bruhn et al., 2000). To further dissociate oscillatory modulation from global state-dependent spectral changes, the aperiodic (1/f) parametrization will also be extracted for each block and examined in relation to BIS values (Donoghue et al., 2020; Lendner et al., 2020).

The impact of CLAS large-scale neural dynamics during general anesthesia will also be quantified through EEG-derived network measures, including functional connectivity (wPLI, Vinck et al., 2011; dPLI, Stam and Van Straaten, 2012) and graph-theoretical properties (network motifs; degree and direction of frontoparietal connectivity; Lee and Mashour, 2018). We will also investigate the effect of CLAS on EEG microstates in order to characterize the temporal dynamics of whole-brain neuronal network.

#### CLAS and nociceptive stimulation

3.7.3

Because nociceptive stimulation will be delivered only during *in-phase*, the primary analyses will assess within-subject changes across the *Pre-Pain*, *Pain*, and *Post-Pain* epochs. As a first step, *δ*-wave morphology will be quantified by comparing amplitude, slope, and power spectral density (PSD) across the three conditions, since these features provide sensitive markers of cortical arousal and nociceptive disruption under anesthesia (Bonhomme et al., 2016; Plourde et al., 2006). To dissociate band-limited power changes from broadband spectral shifts that can occur under propofol anesthesia, we will additionally parameterize the aperiodic (1/f-like) component of the EEG power spectrum for each stimulation block. Power spectral density will be estimated per block and channel, and the aperiodic exponent (slope) and offset will be extracted over a predefined frequency range using spectral parameterization methods. These aperiodic parameters will be compared across *in-phase, anti-phase*, and *sham* conditions and, where relevant, included as covariates when interpreting *δ*-band power changes.

The primary analysis of nociceptive reactivity will be changes in the NOL index and time-to-recovery. Secondary analysis will examine changes in mean arterial pressure (MAP), heart rate (HR), and BIS index values. Source localization and propagation analyses will further characterize the cortical generators and spatiotemporal spread of δ-waves during nociception (Massimini et al., 2004; Murphy et al., 2011).

Statistical models will include linear mixed-effects analyses with Condition (*Pre-Pain*, *Pain*, *Post-Pain*) as a fixed factor and age, and sex. *p*-values will be corrected for multiple comparisons using familywise error correction. This design enables testing whether *in-phase* CLAS can preserve *δ*-wave integrity and stabilize autonomic reactivity in the presence of nociceptive input, a key criterion for balanced anesthesia (Garcia-Larrea and Bastuji, 2018).

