*Specific Aim 2 (SA2): Characterize the effect of in-phase CLAS on depth of anesthesia, as assessed through clinical monitoring tools and high-density EEG*. We hypothesize that *in-phase* CLAS will be associated with EEG and BIS changes indicative of altered anesthetic depth. At the network level, we expect *in-phase* CLAS to be associated with decreased functional connectivity within fronto-parietal circuits, reduced network integration, and increased modular segregation, consistent with a transition toward deeper unconsciousness. Microstate analyses are expected to reveal longer mean durations and reduced repertoire diversity, further reflecting a state of reduced dynamical complexity.

*Specific Aim 3 (SA3): Characterize the effect of in-phase CLAS on δ-waves, in the presence of painful stimulation*. We hypothesize the *in-phase* CLAS will enhance SWA in the presence of nociceptive stimulation, mitigating nociception-induced reductions in *δ*-wave dynamics. We expect this enhancement to be less pronounced than under non-nociceptive conditions, yet sufficient to mitigate nociception-induced reductions in δ-wave dynamics. Specifically, we will assess δ-wave amplitude, slope, frequency, transition frequency, duration, and density, as well as the preservation of spatial coherence across fronto-central regions. Such findings would suggest that CLAS can stabilize cortical δ-waves and counteract arousal-related desynchronization, thereby supporting anesthetic stability and analgesic protection.

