#### Procedures for SA3 (part 2)

2.2.3

Immediately following the completion of Part 1, a 6.5 min *in-phase* stimulation block will be initiated, with simultaneous hd-EEG and pain monitoring using the NOL index, mean arterial pressure and heart rate. The first minute of *in-phase* stimulation will be free of painful stimulation (*Pre-Pain*). A standardized nociceptive stimulation will then be delivered for 30 s (*Pain*). This will consist in a standardized tetanic stimulation to the ulnar nerve of the non-dominant forearm delivered by a routine nerve stimulator (100 Hz, 70 mA; Life Tech - EZstim II) for a duration of 30 s. Measurements will continue during 5 min following painful stimulation (*Post-Pain*). Upon completion, noise-blocking earmuffs, in-ear earphones, and the hd-EEG net will be removed, and study team will exit the operating room. Surgery will begin and anesthetic procedures will continue as standard of care.

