### Secondary hypothesis (H3): CLAS effects on SWA under nociception

4.3

Under nociceptive input, *in-phase* CLAS is expected to partially enhance *δ*-wave dynamics relative to pain without CLAS, though the magnitude of enhancement will be attenuated compared to non-nociceptive conditions. Specifically, under *in-phase* CLAS, δ-wave morphology should recover faster in *Post-Pain*, with amplitude/PSD returning closer to *Pre-Pain* values than expected absent stimulation. At the network level, nociception may interrupt anterior to posterior spread and temporarily reduce inter-regional coherence, whereas *in-phase* CLAS should stabilize these spatiotemporal dynamics, limiting disruption of fronto-central coherence. We also hypothesize that *in-phase* CLAS will buffer autonomic nociceptive responses, yielding smaller increases in NOL, MAP, and HR during tetanic stimulation and faster return toward baseline afterward (Ben-Israel et al., 2013; Edry et al., 2016), without altering anesthetic/analgesic dosing.

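### The painful stimulus is given only under in-phase CLAS, so SA3/H3 can describe the response to pain during CLAS but cannot show that CLAS mitigates, buffers or speeds recovery from it

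*Protocol article*

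**What the plan says.** **Design.** Protocol article, section 2.2.3: Part 2 is one run of in-phase CLAS lasting 6.5 min. The monitoring is described as follows: "stimulation block will be initiated, with simultaneous hd-EEG and pain monitoring using the NOL index, mean arterial pressure and heart rate". After one pain-free minute, "A standardized nociceptive stimulation will then be delivered for 30 s". Then "Measurements will continue during 5 min following painful stimulation". Section 3.7.3 confirms that "nociceptive stimulation will be delivered only during" in-phase CLAS. Section 3.1 lists six conditions in all: in-phase, anti-phase, sham, Pre-Pain, Pain and Post-Pain.

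**Analysis.** Section 3.7.3 plans within-subject comparisons across the three pain epochs. Its mixed models have epoch as the fixed factor, with age and sex. It also plans NOL change and time-to-recovery as the primary analysis of nociceptive reactivity, with MAP, HR and BIS as secondary measures.

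**Claims.**
- SA3 (section 1.8) expects in-phase CLAS to enhance slow-wave activity under pain, "mitigating nociception-induced reductions in" delta-wave dynamics.
- H3 (section 4.3) predicts partial enhancement compared with pain given without CLAS, and amplitude and spectral power nearer to Pre-Pain "values than expected absent stimulation". It also predicts buffered autonomic responses, "yielding smaller increases in NOL, MAP, and HR during tetanic stimulation and faster return toward baseline afterward".
- Section 3.7.3 closes by saying that the design makes it possible to test whether in-phase CLAS can preserve delta-wave "integrity and stabilize autonomic reactivity in the presence of nociceptive input, a key criterion for balanced anesthesia".
- The Discussion (section 5) says that confirmation would demonstrate buffering by CLAS against cortical arousal caused by nociception.

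**The concern.** Each of these claims compares the response to pain with CLAS against the response to pain without it. Only the first is observed, and the article names no external control or reference value for the second.

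A small or short-lived disturbance of delta-waves or NOL would be read as protection by CLAS. It could equally be the usual response to this stimulus at the prevailing propofol level, followed by spontaneous recovery. At stake are the secondary objective, one of the three specific aims, and the main translational conclusion of the Discussion. The limitations in section 6 do not mention the gap.

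**Working it through.** The article gives no power calculation for this aim; section 2.1.2 bases the 30 patients on feasibility, prior literature and the within-subject design. There is therefore no stated figure to reproduce. The question is what the design identifies.

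**1. Is CLAS on throughout Part 2?** The epochs last 1 min + 0.5 min + 5 min = 6.5 min, which is the whole in-phase block. All three pain epochs therefore fall under in-phase CLAS.

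**2. Which effects are identified?** Take a model with seven terms: intercept, in-phase, anti-phase, pain, post-pain, in-phase × pain, in-phase × post-pain. The six conditions are coded as follows.

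| Condition | Int | In | Anti | Pain | Post | In×Pain | In×Post |
|---|---|---|---|---|---|---|---|
| In-phase | 1 | 1 | 0 | 0 | 0 | 0 | 0 |
| Anti-phase | 1 | 0 | 1 | 0 | 0 | 0 | 0 |
| Sham | 1 | 0 | 0 | 0 | 0 | 0 | 0 |
| Pre-Pain | 1 | 1 | 0 | 0 | 0 | 0 | 0 |
| Pain | 1 | 1 | 0 | 1 | 0 | 1 | 0 |
| Post-Pain | 1 | 1 | 0 | 0 | 1 | 0 | 1 |

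The Pain and In×Pain columns are identical, and so are Post and In×Post. The rank is 7 − 2 = 5. The pain effect and the in-phase × pain effect are not estimable separately; only their sum is. The same holds for post-pain.

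**3. What this means for H3.** Suppose amplitude falls by *x* from Pre-Pain to Pain. A pain effect of −*x* with no CLAS interaction fits exactly. So does a pain effect of −2*x* with a protective interaction of +*x*. The data are the same in both cases, and more patients only estimate the sum more precisely. The predicted attenuation of the CLAS effect under pain is this same interaction.

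**4. Can the Part 1 sham block stand in?** It contains no pain, so it adds nothing to the pain columns. It also precedes Part 2 in a fixed order. Section 2.2.2 itself allows that cortical dynamics may deepen over time under a stable infusion, so a comparison across parts mixes pain with elapsed time. The table omits time, which makes it generous to the design.

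**5. What would restore identification?** Adding the Pre-Pain, Pain and Post-Pain rows under sham gives rank 7 of 7, and both interactions become estimable.

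**6. Size of a randomised Part 2.** Alpha and power are assumptions here: two-sided 5% and 80%. With 15 v 15, the normal approximation gives (1.96 + 0.84) × √(2/15) = 1.02; the exact noncentral *t* calculation gives d = 1.06. Adjusting for the Pre-Pain value multiplies this by √(1 − r²). The article gives no r. An assumed r of 0.7 gives 1.06 × 0.714 = 0.76, and r of 0.8 gives 1.06 × 0.6 = 0.64.

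**The case against.** The strongest defence is that SA3 is framed as a characterisation, that section 3.7.3 openly says pain occurs only with in-phase CLAS, and that section 4 presents its contents as literature-based expectations. Pre-Pain is a valid within-subject baseline. Whether delta-waves, NOL, MAP, HR and BIS change with pain under in-phase CLAS, and whether they return, can be estimated. The primary objective rests on Part 1, which ends before any pain. All of this stands, but it supports a descriptive aim only. Disclosing the design does not narrow the claims, and sections 3.7.3 and 5 go beyond expectation in saying what the design can test and what confirmation would demonstrate.

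Three stronger readings are tempting, and the document does not support them.
- A reader might infer that recovery speed cannot be seen at all because Post-Pain is a single five-minute condition. Time-to-recovery is a planned outcome, and nothing says that Post-Pain will be reduced to one average. Recovery can be described; it cannot be attributed to CLAS.
- A reader might infer that the epoch comparison is the only analysis. Section 3.7.3 also lists NOL change, recovery time, and source and propagation analyses.
- A reader might infer that any result would fit H3. A large fall with no return towards Pre-Pain would count against its predicted recovery. The accurate criticism is that a favourable pattern cannot be credited to CLAS.

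**Conclusion.** The point holds: there is no pain-without-CLAS comparator, and the comparative and causal wording of SA3, H3, the closing claim of section 3.7.3 and the Discussion is unsupported as written. This is a failure of identification, with 5 of 7 terms estimable, and not a shortage of power. No analysis plan can recover a condition that is never observed.

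The conclusion rests on the six conditions listed in section 3.1 being complete and on no external reference for pain without CLAS being planned; the article describes none. It does not extend to the within-subject description of the pain response, nor to SA1 and SA2.

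**What to change.** **Restate the aim (wording only).** In sections 1.8, 3.7.3, 4.3 and 5, and in matching text in the Abstract, present SA3/H3 as a within-subject description of how delta-waves, NOL, MAP, HR and BIS change with pain during in-phase CLAS. Remove *mitigate*, *buffer* and *faster*, and the statement that the design enables the test. Add the missing pain-without-CLAS comparator to section 6. The data collection and the planned epoch and recovery analyses can stay as they are.

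**Or obtain the comparator.** If the sponsor wants to keep the comparative claim, the same pain sequence must be observed under sham. One way is to randomise Part 2 to in-phase or sham, with the same single stimulus per patient, and compare Pain and Post-Pain between arms with adjustment for Pre-Pain. This needs a protocol amendment, ethics review under both existing approvals, and a randomisation list. It halves the in-phase-plus-pain sample to 15 and gives up the within-subject contrast for this question. Only large differences would be detectable: about d = 1.06 unadjusted, or 0.76 to 0.64 under the assumed correlations. Whether that trade is worthwhile is for the sponsor to judge.

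### Section 3.7.3 compares δ-band power across the pain epochs but aims its check for broadband spectral change at in-phase, anti-phase and sham, none of which contains pain

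*Protocol article*

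**What the plan says.** Section 3.7.3 (CLAS and nociceptive stimulation) sets the Aim 3 contrast: "the primary analyses will assess within-subject changes across the *Pre-Pain*, *Pain*, and *Post-Pain* epochs". The δ-wave step consists of "comparing amplitude, slope, and power spectral density (PSD) across the three conditions", meaning those three epochs.

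The same paragraph then brings in the aperiodic step. Its purpose is given as "To dissociate band-limited power changes from broadband spectral shifts that can occur under propofol anesthesia", and the commitment is that "we will additionally parameterize the aperiodic (1/f-like) component of the EEG power spectrum for each stimulation block". On the unit: "Power spectral density will be estimated per block and channel". On the comparison: "These aperiodic parameters will be compared across *in-phase, anti-phase*, and *sham* conditions". A further clause allows the parameters as covariates for δ-band power where relevant, without saying at which level. The mixed model at the end of the section has Condition (the three pain epochs), age and sex.

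Section 2.2.3 describes Part 2 as one 6.5 min in-phase "stimulation block will be initiated, with simultaneous hd-EEG and pain monitoring using the NOL index"; all three pain epochs lie inside it. Section 2.2.2 uses *block* for each 3 min Part 1 condition. Section 3.7.2 already plans the step for depth of anesthesia: "the aperiodic (1/f) parametrization will also be extracted for each block and examined in relation to BIS values". Section 3.1 cuts the recording into six segments, with Pre-Pain, Pain and Post-Pain separate.

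**The concern.** The outcome and its safeguard are set on different levels. δ-band PSD is contrasted over three epochs of one stimulation run. The parameters meant to show whether a PSD change is band-limited are contrasted over three other conditions, recorded earlier and without pain. A comparison of in-phase, anti-phase and sham says nothing about the shape of the spectrum during tetanic stimulation.

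At stake is how one part of hypothesis H3 (section 4.3) is read: that amplitude and PSD return towards Pre-Pain values after the stimulus. If nociceptive arousal changed the whole spectrum for 30 s and the change then resolved, raw δ-band PSD could show the same course with no change in δ oscillations. The protocol itself thought this distinction worth making.

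**Working it through.** The plan states no figure on this point, so there is none to reproduce. The check has three parts.

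**1. Levels side by side (section 3.7.3)**

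| Item | Levels or unit |
|---|---|
| δ-band PSD contrast | Pre-Pain, Pain, Post-Pain |
| Aperiodic estimation | per block and channel |
| Aperiodic comparison | in-phase, anti-phase, sham |
| Model terms | Condition (three pain epochs), age, sex |

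No section sets the aperiodic parameters against the pain epochs.

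**2. If *block* means the 6.5 min run**

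Inputs from section 2.2.3: Pre-Pain 60 s, Pain 30 s, Post-Pain 300 s, total 390 s. Shares: 60/390 = 15.4%, 30/390 = 7.7%, 300/390 = 76.9%. One estimate for the run would be mostly Post-Pain.

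Write the model for patient *i* and epoch *e* as y_ie = μ + β_e + γ·x_i + u_i + ε_ie, where x_i is the run-level aperiodic value. Then

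y_i,Pain − y_i,Pre = (β_Pain − β_Pre) + (ε_i,Pain − ε_i,Pre).

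The term γ·x_i cancels. With all three epochs present in every patient, the estimated contrast is the same with or without x_i.

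A simulation on assumed inputs illustrates this: 30 patients, 200 replicates, random intercept, broadband shift 0 / −1.0 / −0.3 over the three epochs, within-patient SD of the offset 0.3, residual SD 0.5, no true band-limited effect.

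| Aperiodic covariate | Mean Pain − Pre-Pain | Rejected at 5% |
|---|---|---|
| none | −1.013 | 100% |
| one value per run | −1.013 | 100% |
| one value per epoch | −0.014 | 3.5% |

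The first two rows differ by at most 3 × 10⁻¹⁵. In a variant where the patient's intercept was correlated with the patient's offset, the run-level covariate again changed nothing. The uncentred epoch-level covariate gave a contrast of +0.67 instead of 0, because its coefficient mixed between-patient with within-patient association. Centring within patient removes the between-patient part.

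**3. How large a broadband effect could be**

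The document gives no exponent, shift or pivot frequency, so all three are assumptions. Take PSD(f) = (f/p)^(−χ) with pivot p. The power ratio over a band from a to b when χ goes from 2.0 to χ′ is

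p^(χ′−2) × [(a^(1−χ′) − b^(1−χ′))/(χ′−1)] / (1/a − 1/b).

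For χ′ = 1.8 and 1–4 Hz: (1 − 4^(−0.8))/0.8 = 0.838 and 1 − 1/4 = 0.75, so the ratio is 1.117 × p^(−0.2).

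| Pivot p | Change in 1–4 Hz power, χ 2.0 → 1.8 |
|---|---|
| 20 Hz | −39% |
| 5 Hz | −19% |
| 2 Hz | −3% |
| 1 Hz | +12% |

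The sign turns where p^0.2 = 1.117, at about 1.7 Hz. For 0.1–4 Hz the ratio is 0.767 × p^(−0.2), from −58% at 20 Hz to −23% at 1 Hz. With a smaller shift, χ′ = 1.9, and p = 20 Hz, the changes are −22% (1–4 Hz) and −35% (0.1–4 Hz). All of this assumes one straight power law over the band, down to 0.1 Hz in the wider case.

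**The case against.** The strongest reply is that *block* is not settled. Section 3.7.3 says PSD itself is estimated per block, and in the same paragraph compares PSD across the pain epochs. If the word always meant the 6.5 min run, the PSD comparison would be impossible too. Section 3.1 provides the three pain epochs as separate segments, so a per-epoch exponent, used under the where-relevant clause, is possible. This stands. A reader might infer that the safeguard cannot work for Aim 3 at all; the text does not support that. The cancellation in the second part of the working follows from one reading of the word and is not evidence for that reading.

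A second reply is that the passage is a Part 1 analysis under the wrong heading: its stated motive is broadband shift under propofol, not under pain, and section 3.7.2 plans a similar extraction. That is plausible, but it leaves Aim 3 with no stated aperiodic analysis in the section where the purpose is announced.

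Third, a condensed article may leave the estimation unit and covariate level to an analysis plan. That is fair for those details. It does not cover the comparison levels, which are stated and do not match the section's own contrast.

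Fourth, the percentages rest on assumptions, and the pivot drives them. This stands in full; they show that the effect could matter, not what it will be.

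**Conclusion.** The point holds in a limited form. Section 3.7.3 states an aperiodic step, names comparison levels that exclude the pain epochs, and lists no aperiodic term in the Aim 3 model. As written, a transient broadband shift during Pain could be reported as loss and recovery of δ power.

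That a covariate would leave the epoch contrast unchanged is conditional on reading *block* as the whole Part 2 run, as section 2.2.3 does. The mismatch in comparison levels does not depend on that reading. The size of any distortion, and its direction for 1–4 Hz, cannot be fixed from the document.

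A reader might also infer that Aim 3 as a whole falls. It does not: the aperiodic clause concerns δ-band power, and the NOL, MAP and HR analyses are untouched. The aperiodic comparison itself suits the Part 1 contrast. The correction should be made before the data are analysed, so that the spectral correction is not chosen after the results are seen.

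**What to change.** In section 3.7.3:

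- Estimate the aperiodic exponent and offset separately for Pre-Pain, Pain and Post-Pain, using the segments defined in section 3.1.
- Compare them across these epochs in the same mixed model as the other Aim 3 outcomes.
- Report δ power after removal of each epoch's own aperiodic fit beside raw δ PSD.
- If an epoch-level aperiodic covariate is used instead, name it in the model and centre it within patient.

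Move the in-phase/anti-phase/sham aperiodic comparison to sections 3.7.1 and 3.7.2, where those conditions are analysed.

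The cost is wording and the same spectral fit run on three segments; no new data are needed. The downside is precision: the Pain epoch lasts 30 s against 300 s for Post-Pain, and at 0.1 Hz it holds only 30 × 0.1 = 3 cycles, so its fit will be noisier. A noisy epoch-level covariate may also under-correct, which is a reason to report raw and adjusted δ power together.
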